#### 6.4 Sample size calculation

For the pair-matched, cluster-randomized design, the sample size of 16 facilities (estimated 3845 patients per facility with a 20% potential for missing records – an estimate of 3076 per facility) over the 4-month recruitment period will have a power of 80% ( $\alpha=0.05$ ) to detect difference of  $\geq 14\%$  for the change in the proportion of patients receiving 3-month refills in the intervention group against the change in the control group (Hayes & Bennett, 1999). The sample size calculation was performed according to the following equation for the comparison of two proportions:

$$c = 2 + \left( z_{\frac{\alpha}{2}} + z_{\beta} \right)^2 \frac{[\pi_0(1 - \pi_0) + \pi_1(1 - \pi_1) + (1 + (m - 1)\rho)]}{m(\pi_0 - \pi_1)^2}$$

The equation was calculated according to the following parameters:

| Parameter                                                     | Value |
|---------------------------------------------------------------|-------|
| Alpha ( $\alpha$ )                                            | 0.05  |
| Power ( $\beta$ )                                             | 0.8   |
| Number of patients per cluster (m)                            | 3076  |
| Estimated change in proportion of 3-month refills ( $\pi_0$ ) | 13%   |
| Estimated change in proportion                                | 1%    |

|                                           |     |
|-------------------------------------------|-----|
| of 3-month refills in control ( $\pi_0$ ) |     |
| Rho                                       | 0.1 |
| J (total, treatment and control groups)   | 16  |

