### *5.3 ART refill length*

One factor affecting facility congestion is the proportion of stable ART patients receiving 3-month refill prescriptions. With longer prescription refill length, as compared to the frequently dispensed 1- or 2-month prescriptions, stable patients are able to space out their facility visits, and thus, reduce the number of people within the facility at any given time. The Zambian ART Guidelines recommend that stable ART patients be provided with prescriptions for up to 3 months at a time, but few patients in Zambia receive such prescriptions.

To assess refill patterns within Zambian facilities, our team conducted assessments at five ART clinics in Lusaka. The majority of patients received their ART refill for one month or less (51%), 26% of patients received a 2-month refill and 23% received a 3-month refill. The decision on the ideal refill length is often decided by a team (including adherence counsellors and clinicians), however the pharmacist made the final decision based their knowledge of drug stock levels. The In-Charge of facilities reported that unreliable stocks of ARTs were the main barrier to the provision of 3-month refills for stable patients.

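### The 80% power claim in section 6.4 is not supported by its own inputs: the text says 14 points, the table says 12, and changes are entered into a variance meant for levels

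*Combined protocol and SAP*

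**What the plan says.** Section 6.4 states that 16 facilities, with "an estimate of 3076 per facility" after allowing for a "20% potential for missing records", "will have a power of 80"% at α = 0.05. The difference to be detected is at least 14%, "for the change in the proportion of patients receiving 3-month refills in the intervention group against the change in the control group".

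The equation is described as one for comparing two proportions. It uses the binomial terms π(1−π), an additive constant of 2 and a design effect 1 + (m−1)ρ. In the text as available, a plus sign stands between the binomial terms and the design effect.

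The parameter table lists "Estimated change in proportion of 3-month refills" as 13% and the matching change "of 3-month refills in control" as 1%. Both rows carry the label π₀. Rho is 0.1 and the total number of facilities is 16.

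Section 6.4 gives no baseline level. The only one in the protocol is in section 5.3, from five Lusaka clinics: "26% of patients received a 2-month refill and 23% received a 3-month refill". Section 6.5 defines the primary analysis as a matched comparison of the change from baseline to endpoint.

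**The concern.** There are two separate problems. The target difference is 14 points in the sentence and 12 points in the table, so the stated power cannot be traced to one set of inputs. More importantly, 13% and 1% are changes over time, whereas π(1−π) is the variance of a yes/no outcome at level π. A clinic whose proportion moves from 23% to 24% does not have the variance of a clinic sitting at 1%. With about 3,000 patients per clinic, between-clinic variance is nearly all of the variance, so this input decides the result.

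The result is meant to inform the Ministry's decision on scale-up (sections 2 and 6.5.4). If power at 14 points is overstated, a null finding could be read as ruling out an effect that the trial had only a moderate chance of detecting.

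**Working it through.** **Inputs.** From section 6.4: two-sided α = 0.05, power 80%, m = 3845 × 0.8 = 3076, ρ = 0.1, 16 clinics (c = 8 pairs), changes of 13% and 1%. From section 5.3: baseline 23%. Then (1.960 + 0.842)² = 7.849; design effect = 1 + 3075 × 0.1 = 308.5; k = 308.5/3076 = 0.1003.

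**1. The plan's formula, with the design effect as a multiplier.** c = 2 + 7.849 × k × [π₀(1−π₀) + π₁(1−π₁)] / (π₁−π₀)². Power at c = 8 is Φ(√(6(π₁−π₀)²/V) − 1.960), where V = k × [sum of binomial terms].

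- Table inputs, 13% vs 1%: sum = 0.1131 + 0.0099 = 0.1230; V = 0.01234; c = 2 + 7.849 × 0.01234/0.0144 = 8.72, so 9 pairs. Power with 8 pairs = Φ(2.646 − 1.960) = 75.4%.
- The text's difference over the tabled control change, 15% vs 1%: sum = 0.1275 + 0.0099 = 0.1374; V = 0.01378; c = 2 + 7.849 × 0.01378/0.0196 = 7.52, so 8 pairs. Power = Φ(2.921 − 1.960) = 83.2%.
- The detectable difference at 80% power with 8 pairs and a 1% control change is 13.1 points.
- The tabled 12 points reaches 80% with 8 pairs only if the constant is 1 instead of the printed 2 (c = 7.72, power 81.6%).

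So 16 clinics can be recovered, but not from the table and equation together.

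**2. What the variance term assumes.** With ρ = 0.1, a control value of 1% implies a between-clinic SD of √(0.1 × 0.0099) = 3.1 points. A control level of 24% (23% + 1%) implies √(0.1 × 0.1824) = 13.5 points. For a 14-point difference, the binomial terms at levels of 24% and 38% sum to 0.1824 + 0.2356 = 0.418, about three times the 0.137 obtained from changes.

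**3. Variance of a clinic-level change.** For baseline level b and endline level e,

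var(change) = k × [e(1−e) + b(1−b) − 2r√(e(1−e) × b(1−b))].

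Assumptions: b = 23%, control endline 24%, intervention endline 38% (36% for 12 points), ρ = 0.1 at both times, 8 pairs analysed at clinic level with t on 7 df (critical value 2.365), and no further credit for matching. The correlation r is not in the documents, so it is varied.

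Worked case, r = 0.8: control 0.1003 × (0.1824 + 0.1771 − 1.6 × 0.1797) = 0.00721; intervention 0.1003 × (0.2356 + 0.1771 − 1.6 × 0.2043) = 0.00861. The sum is 0.01583, SE = √(0.01583/8) = 4.45 points, noncentrality 14/4.45 = 3.15, power 77%.

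| r | pair variance (14 points) | SE (points) | power, 14 points | power, 12 points |
|---|---|---|---|---|
| 0.5 | 0.0389 | 6.98 | 41% | 32% |
| 0.7 | 0.0235 | 5.42 | 60% | 48% |
| 0.8 | 0.0158 | 4.45 | 77% | 64% |
| 0.85 | 0.0120 | 3.87 | 87% | 76% |
| 0.9 | 0.0081 | 3.19 | 96% | 90% |

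Power of 80% needs r of about 0.82 for 14 points and about 0.86 for 12.

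**4. Sensitivity of that threshold (14 points).** At a baseline of 10% the required r is about 0.71; at 50% it is about 0.85. Holding the baseline at 23%, ρ = 0.05 (k = 154.75/3076 = 0.0503) lowers it to about 0.63, and ρ = 0.15 (k = 462.25/3076 = 0.1503) raises it to about 0.88.

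**The case against.** The best defence is that the sentence claims 14 points, not 12, and the plan's own method gives 83% for 14 points over a 1% control change. That stands: the 75% figure exposes a conflict between text and table and does not by itself refute the 14-point claim. It does not rescue the variance on which the 83% rests.

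Three stronger readings are tempting, and the documents do not support them.

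- Taken literally, with the plus sign, the equation gives 56.7 clinics per arm. That cannot be how 16 was obtained. The plus sign is evidently a misprint or a PDF-reading error and says nothing about power.
- Putting levels of 24% and 38% into the plan's equation gives 39% power and a need for 19 pairs. That is an endline-only comparison with no credit for baseline. The plan matches on the baseline proportion (section 6.1) and analyses change from baseline (section 6.5). Only the sample-size formula leaves out the baseline-endline link.
- A reader might infer that the trial is underpowered. Yet the variance implied by the plan's formula at 15% vs 1% (0.0138) equals the difference-in-difference variance at r of about 0.83, which lies inside the range above. Nothing in the documents shows that figure to be too low, or to be right.

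It is also fair that the 23% comes from five clinics and is not limited to stable patients, that enrolled clinics may sit anywhere below 80% (section 6.2), and that section 6.4 does not say whether rho refers to levels or to changes. These are reasons to show ranges.

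**Conclusion.** The 80% figure is unsupported as written. The table's 12 points gives about 75% by the plan's own method, and the 14 points in the text passes only through a variance of the wrong kind. Under the assumptions listed (23% baseline, ρ = 0.1 at both times, 8 pairs, 7 df, no extra gain from matching), power at 14 points runs from 41% to 96% as r goes from 0.5 to 0.9, and the claim needs r of about 0.82 or higher. Because the range spans 80% and r is not given, the finding is a power statement that may or may not hold. It is not a demonstration that 16 clinics are too few. The formula misuse and the text-table conflict are certain; the true power is not.

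**What to change.** Keep the 16 clinics and rewrite section 6.4:

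- Use one target difference in the sentence and the table.
- Replace the plus sign before the design effect with a product, and give the two arms different π labels.
- Base the calculation on the variance of the clinic-level change, with the baseline level, rho (and what it refers to) and r stated as assumptions, and t on 7 df.
- Replace the single 80% claim with power, or detectable difference, over a range of r. On the assumptions above, the detectable difference at 80% power is about 18 points at r = 0.7 and about 13 at r = 0.85.
- Update the baseline level and between-clinic variance from the 16 baseline proportions already being collected (section 6.3.1). A single baseline round does not estimate r, so the range over r should stay.

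The cost is protocol wording and a short recalculation, with no extra clinics or data collection. The downside is that the stated figure may become less favourable.

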## 6.5 Primary and secondary analyses

Firstly, to assess the ability of the matching to produce comparable groups, the characteristics of the matching factors will be compared between the control and intervention group at baseline. Secondly, to assess the presence of other potential confounders, facility-level factors such as the age distribution of the patients or proportion of the population female will be compared between the two groups.

Bivariable comparisons will also compare how these potential confounders are associated with the primary outcome. After examining the success of the matching and the existence of other potential confounders, the remaining analyses will continue with matched analytical methods.

The primary analysis will be a matched comparison of the difference between the intervention and non-intervention facilities in the change of the proportion of eligible patients on 3-month refills overtime (from baseline – endpoint) adjusted for pair-matching and other relevant indicators. The denominator will include all stable patients active in care at the endline. To this end, for bivariable comparisons, we will run McNemar’s matched methods to compare the difference between the proportions between the matched pairs. For further adjustments for potential confounders, conditional multivariable models will be run to examine the difference in the proportion of increased 3-month refills between the intervention and the non-intervention groups.

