## 6 RESEARCH PLAN

### 6.1 Study design

We will conduct a cluster randomised, pair-matched, difference in difference study to assess the impact of the intervention on the proportion of 3-month refill scripts. To assure that the two arms (i.e. the control and the intervention arms) are as comparable as possible, facilities will be matched into pairs based on important factors associated with the primary outcome including the proportion of patients on 3-month refills at baseline, the size of the facility, staff-to-patient ratio (active ART patients) and distance from the Medical Stores Limited (MSL). After pair matching, one facility from each pair will be

randomly assigned to undergo the intervention with a 3-month period of assessment and baseline data collection, followed by a 4-month period of the intervention. To assess facility-level outcomes data will be collected in various formats including patient records, patient exit interviews, provider interviews and other relevant key informant interviews.

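### Section 6.5 names McNemar's test and conditional models without a unit of analysis or any allowance for clinic variation within pairs; run on patients, type I error would be badly inflated

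*Combined protocol and SAP*

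**What the plan says.** Section 6.1 sets the design: "We will conduct a cluster randomised, pair-matched, difference in difference study". Facilities are paired, and within each pair one is randomly assigned to the intervention. Section 6.4 gives "the sample size of 16 facilities", hence 8 pairs, with "an estimate of 3076 per facility" after allowing for missing records. Its formula carries a design effect with rho 0.1.

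Section 6.5 defines the primary contrast as intervention against non-intervention facilities in the change of the proportion on 3-month refills, adjusted for the pairing. Two methods are named. For the bivariable comparison, "we will run McNemar’s matched methods to compare the difference between the proportions between the matched pairs". For adjustment, "conditional multivariable models will be run to examine the difference in the proportion of increased 3-month refills". On covariates it adds: "Bivariable comparisons will also compare how these potential confounders are associated with the primary outcome".

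The section does not say whether the unit in either method is the patient or the clinic. It names no cluster summary, clinic random effect, GEE, robust variance or degrees of freedom based on pairs. Paired t-tests appear only in Section 6.5.1, for secondary outcomes.

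**The concern.** McNemar's test needs one binary result for each member of a matched pair. Here the members are clinics, and each contributes a change in a proportion. No binary clinic outcome is defined, patients in paired clinics are not matched to one another, and a table of discordant pairs has no place for a baseline-to-endline change.

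The conditional models do not repair this. Conditioning on pair removes differences between pairs. Within a pair there is one clinic per arm, so arm and clinic coincide, and any difference between the two clinics is credited to the intervention unless a clinic-level variance is supplied.

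An analyst following the text must therefore choose. Run on patients, the analysis treats thousands of records as independent when 16 clinics were allocated. Run on clinics, it reduces each pair to a sign and discards the size of the effect. The two choices err in opposite directions. The result is meant to inform a Ministry decision on scale-up (Section 6.5.4).

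**Working it through.** **Inputs from the plan.** 8 pairs; m = 3076 (3845 less 20%); rho = 0.1; two-sided alpha 0.05; changes of 13% and 1% (Section 6.4). The pilot proportion on 3-month refills is p = 23% (Section 5.3), so p(1−p) = 0.1771.

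**Assumed, because the plan gives no figure.** The correlation r between a clinic's baseline and endline levels (0.5 to 0.9); the SD s of clinic-specific changes (1 to 10 points); m = 500 as a smaller case, since the primary outcome definition counts only one month's patients. Baseline and endline patients are taken as independent given the clinic.

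**1. The plan's own figure.** Design effect = 1 + 3075 × 0.1 = 308.5. With the design effect multiplied in, c = k + (1.96 + 0.84)² × (0.01×0.99 + 0.13×0.87) × 308.5 / (3076 × 0.12²) = k + 6.72. With k = 1, c = 7.72, so 8 per arm and 16 facilities. With k = 2 and the 14-point difference in the text (15% v 1%), c = 7.52, again 16. The sizing thus allows for clustering, which the named analysis does not.

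**2. Patient-level endline comparison.** The naive standard error is too small by √308.5 = 17.6. Type I error = 2[1 − Φ(1.96/17.6)] = 91%. Simulated null trials with 8 pairs gave 91% for patient-level McNemar with arbitrary pairing of patients, and 92% for the pair-stratified score test of conditional logistic regression. At m = 500 they gave 78–79%.

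The rate depends on the ICC left after matching, which the plan does not give. At m = 3076:
- 0.001: 33%
- 0.0024: 50%
- 0.005: 63%
- 0.01: 73%
- 0.05: 87%

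**3. Patient-level difference in change (the planned contrast), rho applied to the 23% level.**
- Naive SE = √[4p(1−p)/(8m)] = 0.0054 at m = 3076.
- True SE = √{[4·rho·p(1−p)(1−r) + 4(1−rho)p(1−p)/m]/8}.
- At m = 3076, the ratio of true to naive SE is 12.4, 9.7, 7.9 and 5.6 for r = 0.5, 0.7, 0.8 and 0.9. Type I error is 87%, 84%, 80% and 73%.
- At m = 500, type I error is 70%, 62%, 55% and 42%.

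**4. The same contrast, by SD of clinic-specific change, m = 3076.** True SE = √{[2s² + 4p(1−p)/m]/8}. For s = 1 point: √[(0.00020 + 0.00023)/8] = 0.0073, ratio 1.37, type I error 15%. For 2, 3, 5 and 10 points: 35%, 51%, 68% and 83%. Simulation agrees within about a point. For scale, rho 0.1 applied to proportions of 1% and 13% implies SDs of √(0.1×0.01×0.99) = 3.1 points and √(0.1×0.13×0.87) = 10.6 points.

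**5. Clinic-level reading (sign-type test on 8 pairs).** If all 8 agree, p = 2 × 0.5⁸ = 0.0078. If 7 of 8 agree, p = 18 × 0.5⁸ = 0.070. So significance needs all 8, and type I error is about 0.8%. Power under the plan's own variance: the SD of a pair difference = √(0.123 × 308.5/3076) = 0.111. The chance that a pair favours the intervention at 12 points is Φ(0.12/0.111) = 0.86, and 0.86⁸ is about 0.30. At 14 points (15% v 1%) the SD is √(0.1374 × 308.5/3076) = 0.117, the chance is Φ(0.14/0.117) = 0.88, and the power is about 0.37.

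**6. Pair-level paired t-test, 7 df.** Simulated type I error is 4.6–5.2% for endline proportions of 13–40%, and 4.8–5.0% for the difference in change.

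**The case against.** A reader might infer that the plan specifies patient-level models, ignores that clinics were randomised, and would therefore usually declare a null intervention effective. The documents do not support that as stated. Section 6.5 never says its methods run on patients. It frames the contrast between facilities, calls the potential confounders facility-level, and applies McNemar between matched pairs; Section 6.4 sizes the trial with a design effect. On a clinic-level reading the error runs the other way. The patient-level reading is an inference. It is a reasonable one, because McNemar needs binary data and 8 pairs cannot support a multivariable clinic-level model.

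The 91% also needs its conditions. It is for an endline-only comparison at the full rho, whereas the plan analyses change and matches on baseline refill proportion, so the residual ICC may be smaller. For the difference in change, the correlations and SDs are assumptions, and the plan tabulates rho beside changes rather than beside a 23% level. If clinic changes vary by only 1 or 2 points, the rate is 15% or 35%, and at m = 500 with r = 0.9 it is 42%. Usually significant is then not supported, though every one of these rates is far above 5%.

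A reader might also infer that covariates will be selected by their association with the outcome. Section 6.5 says associations will be examined but states no selection rule. What stands is that the adjustment set is not fixed in advance.

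None of this rescues the named test. It does not fit the defined contrast on either reading.

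**Conclusion.** The point holds in conditional form and should be fixed before analysis. McNemar's test cannot estimate or test a difference in change of clinic proportions, and conditioning on pair leaves clinic variation within the pair unaccounted for. What follows depends on a choice the plan does not make. On patients, type I error ranges from roughly three times nominal, if clinic changes barely differ (SD 1 point), to above 80% under the plan's rho with r of 0.8 or less at m = 3076. On clinics as a sign-type test, it is about 0.8%, with power of roughly 30–37% under the plan's own variance against the stated 80%. The exact inflation cannot be fixed from the documents, because they give neither the residual ICC after matching nor the clinic-level correlation over time. The mismatch between method and design rests on neither.

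**What to change.** Replace McNemar in Section 6.5 with a pair-level primary analysis:

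1. For each clinic, compute the endline minus baseline proportion.
2. For each pair, take intervention minus control.
3. Test the 8 differences with a paired t-test (7 df) and report the mean difference with its 95% CI.
4. As a check, run the exact sign-flip test over the 2⁸ = 256 allocations. Its smallest two-sided p is 2/256 = 0.0078, and unlike the sign test it uses the size of each difference.

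Any adjusted analysis should be either a two-stage cluster-level method or a model with clinic effects and small-sample degrees of freedom. Covariates should be named in advance and kept few. The choice between these two is open; stating the unit and the variance is not.

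The cost is SAP wording. No extra data are needed. Confidence intervals will be wider, and honestly so. Power should be restated for 8 pairs: with the design effect multiplied and k = 2, the plan's formula gives about 75% for 13% v 1% and 83% for 15% v 1%.

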## 4 AIMS

The primary aim is to determine the impact of clinic efficiency and supply chain quality interventions on the proportion of stable patients on 3-month refills at 4 months post intervention.

The secondary aims are as follows:

- a) Estimate the effectiveness of improved clinic efficiency and supply chain quality on other factors associated with antiretroviral therapy (ART) outcomes at 4 months post intervention such as patient wait times and patient satisfaction
- b) Assess the factors that enable the intervention to be successful, including qualitative process measures
  - Patient satisfaction and perceptions of quality of care
  - Patient experiences with transition to multi-month refills
  - Patient and clinician perceptions on reliability of supply chain
  - Clinician perspectives on barriers or challenges to providing multi-month refills
  - Compliance to quality improvement standard operating procedures

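### Section 6.5 declares a difference in change as the primary contrast, but the two methods it gives for that contrast estimate other quantities

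*Combined protocol and SAP*

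**What the plan says.** All references are to the combined protocol and SAP.

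- **Declared contrast (6.5).** The primary analysis is a matched comparison of intervention and control facilities "in the change of the proportion of eligible patients on 3-month refills overtime", from baseline to endpoint, adjusted for the pairing and for other indicators that are not listed.
- **Unadjusted step (6.5).** Introduced as the means to that end, McNemar's method is to "compare the difference between the proportions between the matched pairs". Baseline is not mentioned.
- **Adjusted step (6.5).** Conditional multivariable models are to "examine the difference in the proportion of increased 3-month refills between the intervention and the non-intervention groups". The quantity is not defined anywhere.
- **Aim (section 4).** The impact is on "the proportion of stable patients on 3-month refills at 4 months post intervention", which gives an outcome and a time point but no baseline comparison.
- **Sample size (6.4).** The trial is sized "for the change in the proportion of patients receiving 3-month refills in the intervention group against the change in the control group".
- **Outcome (Primary Outcome, under 6.1.3).** It is a clinic's proportion over one month, among stable patients seen in that month.

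**The concern.** An analyst who carries out the two method sentences literally would report one comparison of proportions and one comparison of an undefined increase. Neither is the difference in change on which the trial is declared and sized.

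The literal reading of the adjusted step is also not a net change. According to 5.3, the pharmacist makes the final decision on refill length from knowledge of stock levels, so patients can plausibly move in both directions. A count of upward moves leaves out the downward ones and depends on where the clinic started.

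With only 8 pairs, and a Ministry decision on scale-up resting on the result (6.3.4, 6.5.4), it matters that the computed quantity is the declared one.

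**Working it through.** **1. The plan's own figure.** Inputs from 6.4: m = 3845 × 0.8 = 3076, rho = 0.1, two-sided alpha 0.05, power 80%, 16 facilities (8 per arm). The design effect is 1 + 3075 × 0.1 = 308.5, and (1.960 + 0.842)² = 7.85. With the design effect multiplied in, c = 2 + 7.85 × [p0(1−p0) + p1(1−p1)] × 308.5 / [3076 × (p1−p0)²].

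- Changes of 15% v 1% (the 14-point difference in the prose): c = 7.52, so 8 per arm, which matches the stated 16.
- Changes of 13% v 1% (the table): c = 8.72, so 9 per arm. Power with 8 per arm is 75%.

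The formula as printed adds the design effect instead; with 13% v 1% it gives 56.7 per arm. That, and the gap between 14 and 12 points, are separate matters. What counts here is that 16 is reached by entering changes. The same 12 points entered as endline levels of 36% v 24% (assuming a 23% baseline, and rho carried over) gives c = 24.57, so 25 per arm, and 30% power with 8.

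**2. Level against change.** The simulation uses 8 pairs, with normal within-pair differences at baseline and endline and a two-sided paired t-test (7 df) on the endline difference and on the difference in change. The correlation between baseline and endline differences runs from 0 to 0.8. The ratio is the baseline within-pair SD divided by the endline one; a small ratio means close matching. For the disagreement column, the effect is set to give the change analysis 80% power.

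| Ratio | At least one significant under the null | Verdicts disagree |
|---|---|---|
| 0.2 | 0.057–0.061 | 5–14% |
| 0.5 | 0.073–0.077 | 12–33% |
| 1.0 | 0.085–0.096 | 18–49% |

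A second model assumed a 23% baseline, a 12-point effect and an SD of facility change of 8 to 10 points. Disagreement was about 7% with a baseline SD between pair-mates of 2 points and 38–51% with an SD of 13 points. The value 13 is √(0.1 × 0.23 × 0.77) = 0.133, the case where matching gains nothing.

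**3. The literal share increased.** Assume a 23% baseline (5.3; five clinics, all patients rather than stable ones), the table's net changes of 1 and 13 points, and each patient's refill redrawn independently. Endline levels are then 24% and 36%.

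| | Moved up | Moved down | Net |
|---|---|---|---|
| Control | 0.77 × 0.24 = 18.5% | 0.23 × 0.76 = 17.5% | 1.0 |
| Intervention | 0.77 × 0.36 = 27.7% | 0.23 × 0.64 = 14.7% | 13.0 |
| Difference | 9.2 | −2.8 | 12.0 |

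The upward count shows 9.2 of the 12 points; the rest lies in fewer downward moves.

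As an illustration only, take no intervention effect and a 10-point baseline gap within a pair (23% v 33%). The upward shares are 0.77 × 0.23 = 17.7% and 0.67 × 0.33 = 22.1%, a 4.4-point difference although neither clinic changed.

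**The case against.** A reader might infer that the plan sets up three rival primary contrasts and leaves open which one decides. The documents do not support that. Section 6.5 names the difference in change as the primary analysis, the title, 6.1 and 6.4 agree, and the other two sentences are worded as methods for it.

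Nor are level and change different estimands here. One facility per pair is randomised, so the expected baseline difference is zero and both analyses target the same effect with different precision. The null rates above 0.05 arise only if an analyst sets the declared contrast aside and takes whichever result is significant. Matching on the baseline proportion (6.1) is meant to make the two analyses agree, and the simulation shows that it does so when matching is close.

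The adjusted step may be loose wording for the increase in a clinic's proportion. The outcome is a monthly clinic proportion, and no section describes linking a patient's baseline refill to that patient's endline refill. The 4.4-point illustration assumes a 10-point gap on a matching factor, and randomisation makes the direction of any such gap random, so it adds noise rather than systematic bias.

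All of this stands, and it limits the point to the methods. It does not remove it: declaring a contrast does not help if the stated methods compute something else, and a reader cannot tell loose wording from intent.

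**Conclusion.** The point holds as a mismatch between a declared contrast and its stated methods. McNemar's comparison has no baseline term, the adjusted quantity is undefined, and neither sentence as written yields the difference in change.

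The practical size depends on how well the pairs match at baseline. Level and change verdicts disagree in about 5% of trials with close matching and up to about 49% with none, and the chance that at least one is significant under the null is about 0.057 to 0.096. The within-pair SDs and correlations behind these figures are assumptions. The 9.2 against 12 points rests on the 23% baseline and on independent redraw, and applies only if the adjusted step is read literally.

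The plan should be corrected before analysis. The design itself is not in question.

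**What to change.** In 6.5, replace both method sentences with one estimator. For each of the 8 pairs, take the endline-minus-baseline change in clinic proportion in the intervention facility, minus the same change in the control facility. Test the 8 differences two-sided at 0.05 with a paired (pair-level) test, and state that this is the deciding analysis in place of McNemar's method. A paired t-test on 7 df would do; 6.5.1 already names that test for secondary outcomes.

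Have the adjusted model estimate the same difference in change, with its covariates listed in advance, and label it supportive. Reword the aim in section 4 to refer to the change from baseline to 4 months. Report endline levels descriptively, and report any share of patients moved up together with the share moved down.

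This changes wording in sections 4 and 6.5 and needs no new sites or data for the deciding analysis. It keeps the contrast the sponsor has already declared and used for sizing.
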